**Exclusion Criteria**:

- Farmers who do not meet the inclusion criteria.

A total of 133 participants will be enrolled and randomized.

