**6. Sample Size Calculation**

The sample size calculation for this randomized controlled trial will be based on prior data from a cross-sectional study conducted in the same region, which found that only 4% of farmers routinely read pesticide labels before preparing pesticide mixtures. To achieve a statistically meaningful improvement with our educational intervention, we aim to detect an increase in this behavior by 25%—raising it from 4% to 29%.

Using a significance level of 0.05 and a power of 80%, we estimate that each group (Digital Video-Based Learning Group, Traditional Educational Session Group, and Control Group) will require approximately 35 participants, totaling 105 participants across the three groups. However, we plan to recruit additional participants to account for potential attrition and ensure a robust final sample. The number of these additional participants will be determined based on observed participation and retention rates during the recruitment phase, allowing us to meet our target sample size despite potential dropouts. This approach will help maintain sufficient statistical power throughout the study, even if some participants cannot complete all stages.

7. **Description of the interventions.**

This randomized controlled trial will involve three distinct groups, each receiving different levels of intervention:

1. **Control Group (CG)**
   Participants in the control group will receive no educational intervention and will serve as a baseline to compare the effects of the other interventions. This group will only participate in baseline and follow-up assessments to measure changes in knowledge, practices, and understanding of pesticide labels without external educational support.
2. **Digital Video-Based Learning Group (DVBLG)**

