**8. Materials**

Questionnaire

The data for this study will be collected using a structured questionnaire that has been developed based on a thorough review of relevant literature on pesticide use and safety practices among agricultural communities in Lebanon and internationally (Abou Ibrahim et al., 2023; Dugger-Webster & LePrevost, 2018; Emery et al., 2015). The questionnaire will consist of four primary sections:

1. **Demographics**: This section will capture participants’ age, gender, years of farming experience, and education level.
2. **Pesticide Practices**: Questions will cover prior training on pesticide safety, pesticide handling practices, types of agricultural environments (open field or greenhouse), and the use of personal protective equipment (PPE). Most questions in this section will be closed-ended.
3. **Knowledge**: This section will measure the participants' awareness of the health risks associated with pesticide use, environmental hazards of pesticides, and the importance of PPE. Responses will be collected using Likert scale questions for a range of agreement or knowledge levels.
4. **Pesticide Label Understanding**: This section will assess participants’ ability to interpret pictograms and color codes on pesticide labels. Due to their complexity, open-ended questions will be used to gauge their comprehension.

The questionnaire will be administered face-to-face by trained surveyors proficient in Arabic to ensure clear communication and facilitate accurate data collection. The surveyors will record responses in real-time using Google Docs, which allows for immediate review to minimize data entry errors. To ensure accessibility for all participants, particularly those with low literacy levels, surveyors will read questions aloud and provide clarification as needed.

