**12. Statistical Analysis**

The statistical analysis for this study will be conducted using the Statistical Package for the Social Sciences (SPSS; Chicago, IL, USA), version 25, with statistical significance set at p<0.05p < 0.05p<0.05.

Descriptive Analysis

The baseline characteristics of the participants across the three groups—Control Group (CG), Digital Video-Based Learning Group (DVBLG), and Traditional Educational Session Group (TESG)—will be summarized using descriptive statistics. For continuous variables, such as age and years of experience, we will calculate the mean and standard deviation (SD). For categorical variables, such as gender and prior pesticide training, frequencies and percentages will be presented.

Baseline Comparison

To confirm the comparability of the groups before the intervention, baseline characteristics will be assessed using a one-way analysis of variance (ANOVA) across the three groups, ensuring no significant differences could affect outcome interpretation.

Primary Outcome Analysis (Per-Protocol)

A per-protocol approach will be applied to analyze the primary outcomes, which include knowledge of pesticide safety, interpretation of pesticide labels, and understanding of the environmental impacts of pesticide misuse. The analysis will proceed as follows:

- Within-Group Changes: Paired t-tests will assess changes from baseline to post-intervention for each group.
- Between-Group Differences: A one-way ANOVA will compare differences between the groups in post-intervention scores. If significant differences are detected, post hoc tests (e.g., Tukey’s HSD) will be conducted to explore pairwise comparisons between groups.

Secondary Outcome Analysis

For secondary outcomes, including PPE usage and pesticide-handling practices, changes within each group will be assessed using paired t-tests, while differences between groups will be analyzed using one-way ANOVA with post hoc tests for further analysis as needed.

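### Closed-ended PPE and handling-practice items are assigned only t-tests and pooled-variance ANOVA, so for yes/no items the video-versus-session standard error is wrong whenever the control rate differs

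*Protocol*

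**What the plan says.** Section 12, Secondary Outcome Analysis: "For secondary outcomes, including PPE usage and pesticide-handling practices, changes within each group will be assessed using paired t-tests". Groups are then compared by one-way ANOVA, with post hoc tests as needed. No post hoc method is named for these outcomes. Tukey's HSD appears only as an example, in the primary-outcome paragraph.

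Section 8, on the questionnaire part that covers handling practices and PPE use: "Most questions in this section will be closed-ended".

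Section 6 sizes the trial on a practice, routine label reading, expressed as a proportion: "raising it from 4% to 29" per cent.

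Section 12, Descriptive Analysis: "For categorical variables, such as gender and prior pesticide training, frequencies and percentages will be presented". The next paragraph, Baseline Comparison, says that "baseline characteristics will be assessed using a one-way analysis of variance (ANOVA) across the three groups", with no exception for categorical variables.

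The protocol names no test or model for a proportion.

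**The concern.** The protocol fixes the tests, and they are tests for means. The data they are assigned to are in part categorical by the protocol's own account (gender, prior training) and in part likely to be so (closed-ended practice and PPE items).

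For a yes/no item the variance is p(1 − p), so arms with different rates have different variances. One-way ANOVA and the usual post hoc tests replace the three variances by their average. The control arm's variance then enters the standard error of a comparison in which the control arm takes no part.

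That comparison is video versus session. The hypothesis is that the video is as effective as the session, for practices as well as knowledge. Such a claim is read from the width of the interval for this difference, so a wrong width bears directly on the conclusion.

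**Working it through.** **Inputs.** From section 6: "Using a significance level of 0.05 and a power of 80" per cent; rates of 4% and 29%; "approximately 35 participants, totaling 105 participants across the three groups". From the eligibility section: "A total of 133 participants will be enrolled and randomized", so 133/3 ≈ 44 per arm. The recruitment text gives 150, or 50 per arm. Allocation is equal. Assumption: a yes/no item with control at 4% and both trained arms at 29%. These are the design's own rates for label reading, not PPE rates. Two-sided testing is also assumed, as sidedness is not stated.

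**1. The plan's own figure.** Two proportions, pooled variance under the null, mean rate 0.165:

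n = [1.96 √(2 × 0.165 × 0.835) + 0.8416 √(0.04 × 0.96 + 0.29 × 0.71)]² / 0.25² = (1.029 + 0.416)² / 0.0625 = 33.4, so 34 per group against about 35 stated. The stated size is consistent with a comparison of two proportions.

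**2. Standard error, video versus session.**
- Control variance: 0.04 × 0.96 = 0.0384. Trained-arm variance: 0.29 × 0.71 = 0.2059.
- ANOVA pooled variance: (0.0384 + 2 × 0.2059)/3 = 0.1501.
- Ratio of pooled to true standard error: √(0.1501/0.2059) = 0.854, so 15% too small.
- At 44 per arm, the true standard error is √(2 × 0.2059/44) = 9.7 percentage points and the pooled one √(2 × 0.1501/44) = 8.3. The 95% half-widths (× 1.96) are about 19.0 and 16.2 points.

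**3. Standard error, trained arm versus control.** The true average variance is (0.0384 + 0.2059)/2 = 0.1222. The ratio is √(0.1501/0.1222) = 1.108, about 11% too large.

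**4. Error rates for video versus session when these two arms are equal** (4/29/29%; 200,000 simulated trials per setting):

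| Per arm | Unadjusted pooled: error | Unadjusted pooled: 95% CI coverage | Tukey: error for this pair | Two-arm chi-square: error |
|---|---|---|---|---|
| 35 | 9.5% | 90.5% | 4.7% | 5.0% |
| 44 | 9.8% | 90.2% | 4.6% | 5.3% |
| 50 | 9.7% | 90.3% | 4.6% | 5.1% |

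A normal approximation agrees for the unadjusted case: 1.96 × 0.854 = 1.67, a two-sided error of about 9.4%. Tukey's implied rate for one pair with equal variances is 1.9%.

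**5. Dependence on the assumed rates** (control/video/session, same formula as step 2):
- 4/50/50%: √(0.1795/0.25) = 0.847
- 30/50/50%: √(0.2367/0.25) = 0.973
- all arms equal: 1.00
- 50/90/90%: √(0.1433/0.09) = 1.26, too large

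**6. The other two uses of these tests.** With equal arms, ANOVA on a binary baseline variable had an error of 3.7% to 5.1%, the same as the chi-square test in every setting run (35 and 44 per arm, rates 4% to 50%). The paired t-test on a binary item with no true change had an error of 1.0% to 5.0%.

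**The case against.** **Closed-ended does not mean yes/no.** Items may use frequency scales or be summed, and tests of means suggest that scores are intended. Score construction may also sit in an analysis plan that is not shown. This stands as a limit: for summed scores, t-tests and ANOVA are acceptable and the point falls away. Awareness of the importance of PPE belongs to the Likert knowledge section and is unaffected. But the protocol uses the word scores only for the primary outcomes, does not restrict these tests to scores, and treats the one practice it quantifies as a proportion.

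**Tukey keeps its promise.** At 4/29/29%, video versus session is the only true null, so its 4.6 to 4.7% error is the familywise error, which is below 5%. The 1.9% is an implied rate for one pair, not a level the protocol sets. This stands. The error near 10% needs an unadjusted post hoc test, which the secondary-outcome wording allows but does not prescribe. A separate two-arm test, at 5.0 to 5.3%, would not have a lower error than Tukey.

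**Stronger readings that are not supported.**
- A reader might infer that the interval is always too narrow. Step 5 shows that the direction depends on the rates, and 4% and 29% are planning figures for label reading only.
- A reader might infer that the paired t-tests declare false changes. Their error is not inflated in the settings run.
- A reader might infer that ANOVA misleads on gender or training. It behaves like chi-square there, and frequencies and percentages are already planned.

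**Conclusion.** The point holds for yes/no practice and PPE items. The planned ANOVA gives a wrong standard error for video versus session whenever the control rate differs from the trained arms. At 4/29/29% it is 15% too small: about 9 to 10% error and 90% coverage if the post hoc test is unadjusted, and about 4.7% under Tukey, within its familywise level. At the same rates, each trained arm versus control has a standard error about 11% too large. At other rates the video-versus-session figure ranges from nearly right (0.97) to too large (about 1.26).

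This rests on two assumptions: that items are analysed singly as yes/no, and the rates used. It concerns secondary outcomes, but on the comparison that the hypothesis rests on. ANOVA on categorical baseline variables is an inconsistency of data type, without numerical harm. The wording should be corrected; the trial's size is not affected.

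**What to change.** - State for each PPE and practice outcome whether it is a single item or a summed score. Keep linear models for summed scores only.
- For yes/no items, compare arms by logistic or risk-difference regression on post-intervention status, adjusted for baseline status. Use Fisher's exact test where cells are sparse.
- Report the proportion in each arm and the video-minus-session difference with a 95% CI that does not pool the control arm's variance.
- Describe within-arm change by counts, with McNemar's test if a test is wanted.
- Present gender, education, prior training and other categorical baseline variables as counts and percentages, without ANOVA.

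The cost is a change of wording in section 12. The methods are standard procedures in the software already named, and no further data or participants are needed.

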**12. Handling Missing Data**

Given the face-to-face interview method used to facilitate data entry through Google Docs, missing data is expected to be minimal. However, list-wise deletion will be applied to any remaining incomplete cases to ensure consistency across analyses. This strategy is intended to maintain accuracy while minimizing the impact of missing values on overall findings.

This approach will comprehensively assess intervention effectiveness across comparable groups, consistent with the analysis of the detailed results.

**13. Dissemination of Results**

Study results will be disseminated through publication in peer-reviewed journals and presentations at relevant conferences. A summary of findings will also be shared with the farmers who participated in the study.

**14. Conclusion**

This protocol outlines a rigorous approach to evaluating the effectiveness of WhatsApp-delivered video education in improving farmers' knowledge of pesticide safety and label interpretation. The findings from this study are expected to contribute to the development of scalable and cost-effective educational interventions in resource-limited settings.

